### Outcomes {12}

The primary and secondary endpoints, as well as the parameters of the process evaluation, are presented in Table 1 along with the time points for assessment and measurement methods.

**Table 1 Tab1:** Primary and secondary outcomes UPlusE evaluation

Primary endpoint	Measurement	Time points	Methods
Utilization of services from mental health practitioners/"Early Prevention"	Project-specific questionnaire	From inclusion to U6 checkup	Apps ‘My Paediatric Practice’, ‘My Gynaecology Practice’, all participating parents
Secondary endpoints			
Depression/severity of depression	EPDS (Edinburgh Postnatal Depression Scale)	From inclusion to U6 checkup	Apps (as above), all participating parents
Parent–child bonding	PBQ (Postpartum Bonding Questionnaire)	From inclusion to U6 checkup (child's age of 10–12 months)	Apps (as above), all participating parents
Psychosocial burden	KID-PROTEKT questionnaire	From inclusion to U6 checkup (child’s age of 10–12 months)	Apps (as above), all participating parents
Child regulation	Extended SFS questionnaire	From inclusion to U6 checkup (child’s age of 10–12 months)	Apps (as above), all participating parents
Stigmatization	Project-specific questionnaire	Inclusion and U6 checkup (child’s age of 10–12 months)	Apps (as above), all participating parents
Process evaluation, participant acceptance/satisfaction	Project-specific questionnaire	At U6 checkup (child’s age of 10–12 months)	Apps (as above), parents in the intervention group
Process evaluation, acceptance/satisfaction of participating practices	Project-specific questionnaire	After completion of implementation phase (months 33–35)	Apps (as above), all participating gynaecological and paediatric practices
Process evaluation, acceptance/satisfaction of mental health practitioners/ ‘Early Prevention’	Project-specific questionnaire	After completion of implementation phase (months 33–35)	All involved mental health practitioners/ ‘Early Prevention’ services
Utilization of services in the healthcare system	Analysis of data from the participating health insurance funds	After completion of implementation phase	Data from all participating parents and children
Healthcare system costs in the first year after childbirth	Analysis of data from the participating health insurance funds	After completion of implementation phase	Data from all participating parents and children

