## Data collection and management

### Plans for assessment and collection of outcomes {18a}

The following questionnaires will be used:Socio-demographic questionnaire:Upon study enrolment, comprehensive socio-demographic data will be collected, including age, gender, number of pregnancies and births, history of previous mental health issues, partnership, education, occupation, and financial situation.Edinburgh Postnatal Depression Scale (EPDS):The Edinburgh Postnatal Depression Scale (EPDS), an internationally validated screening instrument for depression [23], will be used. The scale consists of ten self-reported items about depressive symptoms. An EPDS total score of ≥ 10 points indicates a moderate probability of depression, while a score of ≥ 13 points indicates the presence of depression with high sensitivity and specificity [24], also suggesting the presence of anxiety disorders. In UPlusE, an adapted and pilot-tested version of EPDS (EPDS+) [25] will be employed.

The adapted version contains three more questions (‘Plus questions’):Have you ever experienced violence? Yes, quite often. Sometimes. Barely. Never.The birth of my child I experienced as…: Fulfilling. Okay. Unexpectedly difficult/with complications. Traumatizing.I have experienced my pregnancy (so far) as: Burdensome/tense. Rather burdensome/tense. Rather positive/relaxed. Positive/relaxed.

The ‘Plus questions’ do not influence the EPDS score, rather they can be interpreted as a short screening for traumatic experiences in addition to the screening for depressive symptoms [25].

3.KID-PROTEKT:The KID-PROTEKT questionnaire [3] will be used as a measuring instrument for parental psychosocial burdens. The questionnaire includes six items about personal stress situations. A score ≥ 1 is considered a basis for conversation to determine if there is a need for support .4.Postpartum Bonding Questionnaire (PBQ):Additionally, the scale 1 (impaired bonding) of the Postpartum Bonding Questionnaire (PBQ) with 12 items will be used. Overall, the PBQ is a simple and well-validated instrument for assessing impaired parent-to-child bonding. The scale 1 is a general factor that signals the likelihood of a relationship problem at a threshold (cutoff value) of 12 points [26]. Responses to each of the 12 items will be given on a 6-point Likert scale (‘always’, ‘very often’,

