## Statistical methods

### Statistical methods for primary and secondary outcomes {20a}

The intervention in UPlusE will be scientifically evaluated using a multidimensional approach and various methods (multilevel analyses, process analyses, secondary data analysis) that, in combination, allow for a comprehensive assessment of different aspects of the project.

All data analyses will be conducted using pseudonymized data. After the observation period (U6), the primary and secondary endpoints for parents with psychological and psychosocial issues will be analysed in a group comparison (comparison between the intervention and the control group). Multilevel analyses will be conducted based on the intention-to-treat principle.

Additionally, the trajectory of values and the utilization of services for parents without psychological and psychosocial issues at the time of project inclusion (clinical evaluation) will be descriptively analysed. Quantitative parameters will be analysed using multilevel analyses to correct for cluster randomization. In the case of structural inequality between the intervention and control groups, relevant parameters (such as age, gender, number of pregnancies and births, partnership, socioeconomics—education, occupation, financial situation, severity of depression) will be adjusted for. All tests will be two-tailed with a significance level of alpha = 0.05.

In the analysis, a descriptive evaluation (e.g. symptom severity, child symptoms, service utilization) will be conducted for the group of parents who were positively screened. At the time of U6, a comparison between the intervention and control groups will be performed (e.g. symptom severity, parent–child bonding, child symptoms). Furthermore, across groups, psychosocial stress, depressive symptoms, stigma, and service utilization will be assessed.

The data from the process analysis questionnaires will be analysed descriptively and inferentially.

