### Interim analyses {21b}

After the recruitment phase is completed, baseline assessments will be performed. Particularly relevant here is the analysis of structural equivalence among participants from the intervention and control practices.

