### Methods in analysis to handle protocol non-adherence and any statistical methods to handle missing data {20c}

As this is a study in a healthcare setting and not a clinical trial testing a clinical procedure or medication, protocol non-adherence is not relevant here. For intention-to-treat analyses, it may become necessary to impute missing data because the intention-to-treat analysis includes all participants, regardless of their adherence to the study. If (potentially multiple) imputation of missing data will be required, it will be carried out especially in the analysis of the primary research question. Scores will be imputed, not individual items, and this will be done separately for each outcome or research question. For per-protocol analyses, missing data will not be a concern, as only participants who have completed all necessary measurements will be considered here. If significant group differences will occur at baseline, the inverse probability weighting procedure may become necessary.

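### History of mental health problems, recorded at enrolment, is missing from the illustrative adjustment list and is not secured as a covariate of the primary model

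*Protocol article*

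**What the plan says.** All references are to the Protocol article.

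- **Adjustment ({20a}).** It is conditional. The trigger is worded as "In the case of structural inequality between the intervention and control groups". The variables are then introduced as examples and not as a closed list: "relevant parameters (such as age, gender, number of pregnancies and births, partnership, socioeconomics—education, occupation, financial situation, severity of depression) will be adjusted for".
- **Enrolment data ({18a}).** The socio-demographic questionnaire covers "age, gender, number of pregnancies and births, history of previous mental health issues, partnership, education, occupation, and financial situation".
- **Baseline check ({21b}).** Baseline is examined once recruitment is complete: "Particularly relevant here is the analysis of structural equivalence among participants from the intervention and control practices". No variables are listed.
- **Weighting ({20c}).** "If significant group differences will occur at baseline, the inverse probability weighting procedure may become necessary". Again no variables are listed. The same section allows imputation, done separately for each outcome.
- **Primary endpoint ({12}, Table 1).** Self-reported use of mental health practitioners or Early Prevention services between inclusion and U6. The eligibility criteria ({10}) do not exclude earlier or current treatment, and {11d} prohibits no concomitant care.
- **Allocation and enrolment.** Practices are randomised once their physicians have confirmed participation ({16a}), doctors recruit and enrol parents ({26a}), and the trial is open ({17a}).

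**The concern.** The adjustment list follows the enrolment questionnaire item by item, leaves out one item and adds severity of depression. The item left out is the only one in that questionnaire that concerns earlier mental illness, while the endpoint is use of mental health or support services. Parents who have been ill before plausibly know the services and how to reach them. Some may already be in treatment at enrolment and could be counted as users in either arm.

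Two things are at stake. The first is precision: a predictor already in the database is used only if an imbalance happens to be seen. The second is a choice that depends on the data. The list is open and its use is triggered by observed differences, so someone decides after seeing baseline data whether history enters the primary model. That is an avoidable weakness in an open cluster trial where enrolment follows allocation, because the case mix of the arms can differ by more than chance.

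**Working it through.** **Step 1. Compare the two lists.**

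| Variable | Enrolment questionnaire {18a} | Named for adjustment {20a} |
|---|---|---|
| Age | yes | yes |
| Gender | yes | yes |
| Pregnancies and births | yes | yes |
| History of mental health problems | yes | **no** |
| Partnership | yes | yes |
| Education | yes | yes |
| Occupation | yes | yes |
| Financial situation | yes | yes |
| Severity of depression | no (EPDS, separate instrument) | yes |

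Seven of the eight enrolment items are named; history is the only one that is not.

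**Step 2. Does severity of depression stand in for history?** Only in part. Under {11a}, a parent can screen positive through PBQ-1 (12 or more) or KID-PROTEKT (1 or more) with an EPDS score below 10. Such parents have a low current depression score by definition, whatever their history.

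**Step 3. Reproduce the plan's own figures ({14}).** The inputs are 15% against 25%, two-sided alpha 0.05 and power 0.80. With mean proportion 0.20, n per arm = [1.96·√(2·0.20·0.80) + 0.8416·√(0.15·0.85 + 0.25·0.75)]² / 0.10² ≈ 250, so 500 in total, as stated. Then 500 × 1.725 / 0.80 = 1,078, also as stated. Evaluable positives: 1,078 × 0.80 ≈ 862, or 431 per arm.

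**Step 4. Variance explained by history.** The article gives no figure for how common a history is or how strongly it predicts use, so these are assumptions: prevalence h of 20–40% among positively screened parents, and use that is RR = 2–4 times as frequent with a history. Overall control use is the article's 15%.

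Use without history: p0 = 0.15 / (1 − h + h·RR). Use with history: p1 = RR·p0. Share of variance: R² = h(1 − h)(p1 − p0)² / (0.15 × 0.85). Shift from a 10-point imbalance: 0.10 × (p1 − p0).

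| h | RR | p0 | p1 | R² | Shift (points) |
|---|---|---|---|---|---|
| 0.2 | 2 | 0.125 | 0.250 | 0.020 | 1.25 |
| 0.2 | 3 | 0.107 | 0.321 | 0.058 | 2.14 |
| 0.2 | 4 | 0.094 | 0.375 | 0.099 | 2.81 |
| 0.3 | 2 | 0.115 | 0.231 | 0.022 | 1.15 |
| 0.3 | 3 | 0.094 | 0.281 | 0.058 | 1.88 |
| 0.3 | 4 | 0.079 | 0.316 | 0.092 | 2.37 |
| 0.4 | 2 | 0.107 | 0.214 | 0.022 | 1.07 |
| 0.4 | 3 | 0.083 | 0.250 | 0.052 | 1.67 |
| 0.4 | 4 | 0.068 | 0.273 | 0.079 | 2.05 |

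So R² is about 2–10%. Read crudely as sample size, that is 1,078 × 0.020 ≈ 20 to 1,078 × 0.099 ≈ 107 positives. This is history on its own; the increment is smaller if severity of depression is also in the model and carries part of the same information.

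**Step 5. Imbalance by chance.** The 95% range is 1.96·√(2h(1 − h)/431)·√DE. As design effect DE I take both the stated 1.725 and the value that the stated ICC and cluster size give, 1 + (2.5 − 1) × 0.15 = 1.225. (That mismatch is a separate matter and does not affect this point.) The result runs from 5.9 points (h = 0.2, DE 1.225) to 8.6 points (h = 0.4, DE 1.725). An imbalance of that size would move the utilization difference by about 0.7–2.0 points.

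**Step 6. Imbalance through open enrolment.** A 10-point imbalance, which is a scenario and not a forecast, shifts the difference by 1.1–2.8 points (last column above) against the planned 10. A 5-point imbalance shifts it by half as much, 0.5–1.4 points.

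**The case against.** The case against is substantial.

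*The list is open.* The words 'such as' make it illustrative. Nothing excludes history, and both the baseline check in {21b} and the optional weighting in {20c} are open to any variable. A reader might infer that history stays unadjusted even when adjustment is made. The text does not support that. What stands is narrower: adjustment for history is possible but not secured.

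*A large imbalance would be noticed.* At h = 0.3, a 10-point difference lies 2.4–2.9 standard errors from zero (DE 1.725 and 1.225), so the planned check should flag it and adjustment would follow. A reader might also take from a null simulation that the plan has a type I error of about 12%: with h = 0.3, RR = 3 and a 10-point imbalance, about 12% of runs rejected without history in the model and about 5% with it. The higher figure belongs to a model with no adjustment at all, not even for severity, and so does not describe the plan's analysis under that imbalance. It should not be quoted as the plan's expected error rate.

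*The premises are not documented.* No section ranks predictors of service use. The severity score steers the recommended service in {11a}, and it is listed. The endpoint also includes Early Prevention, where psychiatric history may matter less. The Discussion says physicians often miss parents' psychological burdens, which weakens the idea that they enrol selectively on known history. All of this is fair. It means that history can be called a plausible strong predictor, not the strongest, and that selective enrolment is a possibility, not an expectation. Without selection, leaving history out costs precision and does not bias the comparison.

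*The final covariate list belongs in an analysis plan.* An analysis plan that is not shown may well settle this. But the article states a rule, adjustment triggered by observed imbalance from an open list, and that stated rule can be improved whatever the other document says.

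**Conclusion.** The point holds as an improvement to the stated method, not as an error that invalidates the analysis. History of mental health problems is the only enrolment variable not named for adjustment, and its use in the primary model hangs on a decision made after baseline data are seen. Fixing it in advance would mainly gain precision, about 2–10% of outcome variance for history alone. It would also protect the comparison if open enrolment unbalanced this factor, where a 10-point imbalance is worth about 1.1–2.8 points against the planned 10. Both ranges rest on assumed values (history in 20–40%, use 2–4 times as frequent) that the article neither gives nor contradicts. No stated figure changes.

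**What to change.** In {20a}, name history of previous mental health problems, as recorded at enrolment, as a fixed covariate of the primary multilevel model, in every version of that model and regardless of observed imbalance. In {20c}, state that it also enters any inverse probability weighting or imputation model. Merely adding it to the existing conditional list would not secure the precision gain and would leave the data-dependent choice in place. If an analysis plan already specifies this, align the protocol wording with it.

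The cost is a sentence of text and one model term. The variable is already collected, so no new data and no change to the sample size are needed.

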### Interim analyses {21b}

After the recruitment phase is completed, baseline assessments will be performed. Particularly relevant here is the analysis of structural equivalence among participants from the intervention and control practices.

### Methods for additional analyses (e.g. subgroup analyses) {20b}

As sensitivity analyses, per-protocol analyses will also be conducted. Per-protocol analyses consider only the results of those patients who received the intervention according to the study protocol. In the UPlusE project, per-protocol analysis will be performed with data from patients who were positively screened and actually sought assistance.

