**Methods:**

UPlusE is a prospective, cluster-randomized controlled trial conducted in an outpatient setting. Obstetric and paediatric practices will be randomized into an intervention and control group (1:1 ratio). Practices and enrolling patients will be required to use specific smartphone apps (practice apps) for interaction. The screening will occur with the apps at each paediatric checkup up to the child’s age of 12 months, using the Edinburgh Postnatal Depression Scale (EPDS), KID-PROTEKT questionnaire, and the scale 1 (impaired bonding) of the Postpartum Bonding Questionnaire (PBQ-1). The goal is to screen 10,000 patients across Germany. Gynaecologists and paediatricians will receive certified training on peripartum depression. Participants in the intervention group with scores above cut-offs (EPDS ≥ 10, KID-PROTEKT ≥ 1, PBQ-1 ≥ 12) will receive counselling through their treating gynaecologists/paediatricians and will be provided with regional addresses for psychiatrists, psychotherapists, and “Frühe Hilfen” (early prevention) as well as family counselling centres, depending on symptom severity. At each screening, participants will be asked whether they sought support, where, and with whom (utilization). Utilization is the primary outcome.

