
## Objectives {7}

The overall goal of UPlusE is to increase the utilization of treatment and counselling services for mothers and fathers experiencing perinatal depression, psychosocial distress, or impaired bonding preceded by a low-threshold screening for these conditions. Within UPlusE, the term psychosocial stress encompasses both psychosocial stress and impaired bonding. The main research question of the UPlusE project is: can the utilization of any support services by parents with psychological or psychosocial issues be improved through the low-threshold intervention? The working hypothesis is: there is a significantly higher utilization of support services in the intervention group between enrolment in the project and the U6 checkup (child’s age of 10–12 months) compared to the control group.

Additional secondary research questions:For parents positively screened for peripartum depression or psychosocial distress (in the following meant as psychosocial distress and impaired bonding):aWhat mental health services are utilized? What is the proportion of medication-based therapies? How quickly do they receive treatment?bHow frequently do various forms of child regulatory problems occur in this group?cDo child regulatory problems occur with varying frequency in families with different stress profiles (mental illness/psychosocial burdens)?

Sensitivity analyses will investigate the following questions:iv.Is the proportion of parents experiencing an improvement in depressive symptom severity higher when utilizing mental health services?v.Is the proportion of parents with an unaffected parent–child relationship higher when utilizing mental health services?vi.Do child regulatory problems occur less frequently in parents utilizing mental health services?

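### The per-protocol set is defined by having sought help, which is the trial's primary outcome, and not by having received the intervention

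*Protocol article*

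**What the plan says.** Section {20b} of the protocol article has three consecutive statements.

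- The role of the analysis: "As sensitivity analyses, per-protocol analyses will also be conducted".
- The principle: "Per-protocol analyses consider only the results of those patients who received the intervention according to the study protocol".
- The set itself: "per-protocol analysis will be performed with data from patients who were positively screened and actually sought assistance".

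On the outcome, the Abstract (Methods) says that "participants will be asked whether they sought support, where, and with whom (utilization). Utilization is the primary outcome". The utilization questionnaire in section {18a} records by self-report whether the parent has sought treatment or counselling. Table 1 in section {12} gives the primary endpoint as use of mental health practitioners or Early Prevention services from inclusion to U6.

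On the intervention, section {8} describes screening plus, where needed, a consultation with the treating doctor. Section {11a} adds release of the result, recommendations and regional addresses. Section {11b} leaves parents free to accept or decline help.

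Two other places bear on the point. Section {20c} says: "For per-protocol analyses, missing data will not be a concern, as only participants who have completed all necessary measurements will be considered here". Section {7} lists questions iv to vi as sensitivity analyses among screen-positive parents; the first is: "Is the proportion of parents experiencing an improvement in depressive symptom severity higher when utilizing mental health services". The primary analysis in section {20a} is an intention-to-treat multilevel comparison of the arms.

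**The concern.** The second and third statements in section {20b} describe different groups. A parent who was screened, given the result, counselled as planned and then declined help has received the whole intervention, yet falls outside the set. Declining is not a deviation, because section {11b} allows it. A control parent who found help unprompted falls inside the set, although that says nothing about adherence to the control condition.

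The third statement conditions on the event that the trial counts as its primary outcome. An analysis in such a set cannot support or challenge a result on utilization. On the secondary endpoints it replaces the randomized comparison with one between two self-selected groups, so arm is mixed with severity and motivation. The Discussion expects the trial to show gains in mental health, bonding and child regulation, and those are the endpoints that this selection could distort.

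**Working it through.** **1. The plan's own figures.** Inputs from section {14}: 15% v 25%, power 0.80, design effect 1.725, dropout 20%. Two-sided alpha 0.05 is from section {20a}.

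Per arm, with pooled variance: n = [1.96 × √(2 × 0.20 × 0.80) + 0.842 × √(0.15 × 0.85 + 0.25 × 0.75)]² / 0.10² = (1.109 + 0.472)² / 0.01 ≈ 250, so 500 in total. Then 500 × 1.725 / 0.80 = 1078. Both stated figures are reproduced. (The design effect is a separate matter: 1 + (2.5 − 1) × 0.15 = 1.225, not 1.725. It changes the counts below but not the share.)

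**2. Is the set tied to the intervention or to the outcome?**

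| Item | Where | Content |
|---|---|---|
| Intervention | {8}, {11a} | Screening, result, advice, addresses |
| Primary outcome | Abstract, {18a} | Whether support was sought |
| Per-protocol principle | {20b}, second statement | Intervention received |
| Per-protocol set | {20b}, third statement | Screen-positive and help sought |

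The last row matches the second and not the third.

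**3. Effect on utilization, if the set is used for it.** Let p_C and p_I be the true utilization rates. Within the set, P(used | used) = 1 in each arm, so the difference is 1 − 1 = 0 for any p_C and p_I. If the help-seeking condition were applied to the intervention arm only, the comparison would be 100% v about 15%, which is equally uninformative. The overlap may fall short of complete, because section {18a} also records general practitioners and other sources that Table 1 does not name. What remained would then reflect which provider was chosen, not whether help was sought.

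**4. How much of the comparison remains, on planned rates.**

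- After dropout: 1078 × 0.80 = 862.4, or 431.2 per arm.
- Control: 431.2 × 0.15 = 64.7. Intervention: 431.2 × 0.25 = 107.8.
- Total: 172.5 of 862.4 = 20%, which is (0.15 + 0.25) / 2.

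These counts are illustrative. Section {14} states the 15% and 25% for mental health services, whereas the endpoint also includes Early Prevention. The 1078 is a required number linked to depression prevalence, whereas a positive screen also includes KID-PROTEKT ≥ 1 or PBQ-1 ≥ 12. If the 30% with psychosocial stressors in section {6a} applied, 10,000 × 0.30 = 3,000 would be positive. At the same rates and dropout that gives 1,200 × 0.15 = 180 v 1,200 × 0.25 = 300, again 20%.

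**5. Secondary endpoints.** The document gives no relation between severity and help-seeking, so the bias cannot be sized from it. For illustration only, assume standard normal baseline severity, a logistic model for help-seeking calibrated to 15% and 25%, and no effect of the intervention on severity. The difference in mean severity between help-seekers (intervention minus control) is then:

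| Log-odds slope per SD, control / intervention | Difference (SD) |
|---|---|
| 0 / 0 | 0 |
| 0.5 / 0.5 | −0.05 |
| 1.0 / 1.0 | −0.11 |
| 1.5 / 1.5 | −0.16 |
| 1.0 / 0.5 | −0.39 |

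Under these assumptions a difference in favour of the intervention appears with no true effect. In these scenarios it vanishes only when help-seeking is unrelated to severity.

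**The case against.** The strongest reply is that the protocol nowhere says the per-protocol analysis covers the primary endpoint. The only sensitivity questions that it lists, iv to vi in section {7}, concern depressive symptoms, the parent-child relationship and child regulation. A reader might infer that the trial plans an empty comparison of utilization. The text does not establish that. It sets no restriction either, so the possibility stays open, and for secondary endpoints the selection problem applies regardless.

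Second, the intention-to-treat analysis carries the main conclusion and does not depend on this set. That stands, and it limits how serious the point is.

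Third, questions iv to vi ask what accompanies service use among screen-positive parents and claim no randomized contrast. That also stands: the fault there is the label, and the need for adjustment.

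Fourth, in a set of completers there is nothing to impute, so the missing-data sentence is literally correct. That is so, but completion is itself a selection, and the sentence presents it as though the problem were gone.

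Finally, restricting a corrected set to parents positive at enrolment would contradict section {11a}, under which those who turn positive later receive the recommendations from then on. The article also describes no record of counselling. The fix has to respect both.

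**Conclusion.** The point holds as a fault in a supplementary analysis. Section {20b} contradicts itself and selects on the outcome. Used for utilization, the set gives 100% v 100%, or close to it, whatever the truth. Used for EPDS, PBQ or SFS outcomes, it gives a comparison selected after randomization, with a bias of unknown size. On the planned rates about one fifth of screen-positive parents would remain; that share rests on 15% and 25% being the rates of entry into the set.

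Three stronger readings are not supported: that the primary result is compromised, that about 65 v 108 is the expected size of the set, and that the overlap with the Table 1 endpoint is exactly complete. The correction should be made before outcome data are analysed, but it is not a condition for the validity of the primary analysis.

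**What to change.** Define the per-protocol set by delivery and leave help-seeking out of the definition.

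- Intervention arm: screen-positive at any screening up to U6, with the result and recommendations released, and the consultation given where this is already recorded.
- Control arm: screen-positive at any screening, with no result released before U6 apart from the immediate-notification rule in section {11b}.
- If delivery cannot be established from existing app data, drop the help-seeking set as a sensitivity analysis of the arm comparison.

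A delivery-based set is still formed partly after allocation, so it remains supplementary; it is no longer conditioned on the outcome.

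Label questions iv to vi in section {7} as observational associations with service use, adjusted for enrolment EPDS and history of mental health problems, both already collected. In section {20c}, replace the claim about missing data with a statement that restriction to completers is a further selection.

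The cost is wording and a small amount of extra analysis, with no added participants and no new data collection. The supplementary analysis may also look less favourable than one confined to help-seekers.
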